### Data collection methods

Database management is delegated to the Munich Study Center, Munich, Germany (MSZ). First, data management and data verification plans were generated, followed by the creation of a validated study database using the platform EDC-System Macro (Elsevier, London, UK). Data electronically available in the anesthesia protocol is transferred into the database using a validated process. Screening, medical history, and PACU data is entered manually into the database by unblinded study staff. Blinded outcome data is entered in specified study iPads (Apple Inc., Cupertino, CA, USA) using FileMaker 16 Go (Claris International Inc. c/o Apple, Santa Clara, CA, USA) with a validated transfer process into the study database.

There is a prespecified monitor plan in place, including five on-site visits and remote monitoring every 6 weeks. Execution is delegated to the MSZ. On-site monitoring consists of source data verification and source data review, while data review will be performed remotely. The frequency of visits can be adapted in case of significant recruitment delays or other issues arise.

All study database users receive required training applicable to their role in the conduction of the trial. The completion of this training is tracked and attested by an instructor, who also review and verify the appropriate conduction of the trial and adherence to data accuracy and security goals.

### Data management

All data entered into the database is reviewed. Data cleaning is planned in three rounds to resolve discrepancies, search for missing data, and declare them as not available should no solutions be found. Furthermore, protocol violations are identified and classified. Withdrawal of the consent before anesthesia, i.e., before recruitment and intervention, is reported in the CONSORT diagram only. Withdrawal of the consent after intervention is also reported, but will not affect the study related analysis of the already collected data, as well as all safety-related events even after withdrawal. Loss of contact information may result in loss of follow-up information, which can be reduced through inquiries to the respective municipal registration offices.

The database will be locked and exported for statistical analysis. At this stage, permission for access to the database will be revoked for all investigators, and the database will be archived.

Missing information on the outcome variables, irrespective of the reason, results in the exclusion of a patient. If more than 5% of patients are excluded from the primary analysis, the study aim cannot be reached.

### Statistical methods

The statistical analysis plan is described in the study protocol. This version and its amendments are published at http://www.superadd.de, and any further updates will be made available there. After closing of the database, no changes to the analysis plan will be allowed.

Scaled variables will be presented, depending on their distribution, as mean and standard deviation or median and interquartile range. Categorical variables will be represented as numbers and frequencies.

Statistical analyses will be performed for all given outcomes, irrespectively of any protocol violation (intension-to-treat analysis). In case of major protocol violations or discontinuation due to treatment-specific complications, an exploratory patient-per-protocol analysis will be performed, excluding the respective patients.

The primary endpoint is the incidence of any postoperative complications graded as Clavien-Dindo ≥ 2. The two treatment groups will be compared using a two-sided *χ*^2^ test for independent samples regarding the incidence of any postoperative complication. The results will be presented as absolute risk reduction based on the Mantel-Haenszel risk differences and its improved confidence interval estimate [25]. Sub-groups analyses and adjustments will be included for risk groups according to ASA status, preoperatively existing vs. intraoperatively acquired hypalbuminemia, and varying surgical interventions. Exploratory comparisons will be performed of each component of the Clavien-Dindo, as well as each domain of the POMS. Scaled surrogate variables of fluid therapy, such as creatinine concentration, vasopressor infusion rates, or need for supplementary oxygen during PACU, will be compared with either *t* tests or Mann-Whitney *U* tests, according to the distribution of the variable.

Statistical significance will be assumed at an alpha level of 0.05. Statistical analyses will be conducted using Statistical Package for the Social Sciences 26.0 (IBM SPSS Statistics, Chicago, IL, USA).

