### Sample size

The frequency of complications graded as Clavien-Dindo Score > 2 in surgical patients with preoperative hypalbuminemia has been reported as 52%, compared to 23% in patients with normal albumin concentration, according to an observational study in patients with ovarian cancer [3]. We assumed a clinically relevant treatment effect if albumin substitution could halve the absolute risk difference between patients with hypalbuminemia and normal albumin, i.e., an absolute risk reduction of 14% or a relative risk reduction of approximately 25%. Since a general surgical population was likely to have a different risk of complications related to hypalbuminemia, an interim analysis was planned after 100 patients, so as to better estimate the risk of complications in the study population and recalculate the sample size using a 25% relative risk reduction.

After inclusion of 100 patients, an independent statistician compared the two treatment groups for the incidence of any postoperative complications graded as Clavien-Dindo ≥2 and > 2, using a two-sided *χ*^2^ test for independent samples. Had the difference between groups reached a significance level of 0.002, the study would have been terminated. Since the incidences of complications graded as Clavien-Dindo ≥ 2 after 100 patients were 82% vs. 84% (*p* = 0.79) and those scored Clavien-Dindo > 2 were 34% vs. 36% (*p* = 0.83), the study must be continued. Hence, the 95% confidence interval of the relative risk for complications graded Clavien-Dindo ≥ 2 includes the postulated 25% relative risk reduction (0.87 [0.37–2.03]), the interim analysis also failed to show a missing treatment effect, which would also terminate the study. Based on incidences of the interim analysis, a significance level of 0.048, and a power of 80%, a sample size of 4408 patients would be required to prove significance. In fact, the study was limited to 300 patients per group, according to the prerequisite given by the responsible authority, the Paul-Ehrlich-Institut. Based on the limited number of 2 × 300 patients, the frequencies of complication of 82% and 84% and a significance level of 0.048, the power would be 50%.

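### The Statistical methods section sets alpha at 0.05 with no exception for the primary test, whereas the Sample size section pairs a 0.002 interim stopping level with 0.048 for the final analysis (minor)

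*Protocol article*

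**What the plan says.** The Sample size section describes a between-group comparison after 100 patients with a stopping rule: "Had the difference between groups reached a significance level of 0.002, the study would have been terminated". The comparison covered two gradings; the independent statistician "compared the two treatment groups for the incidence of any postoperative complications graded as Clavien-Dindo ≥2 and > 2". The section then plans the rest of the trial at a reduced level. For the recalculated size it uses "a significance level of 0.048, and a power of 80%, a sample size of 4408 patients would be required to prove significance". The power statement for 300 patients per group uses 0.048 again.

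The Statistical methods section specifies the final primary analysis: "The two treatment groups will be compared using a two-sided" chi-squared test of the incidence of complications graded Clavien-Dindo 2 or higher. After listing subgroup, exploratory and surrogate-variable comparisons, it ends with "Statistical significance will be assumed at an alpha level of 0.05". It does not mention 0.048, 0.002 or the interim look.

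**The concern.** The interim look could have stopped the trial on a between-group difference, so it is one of two routes to a false-positive result. The Sample size section treats it that way: 0.048 is what remains of 0.05 once 0.002 has been set aside. The only sentence that sets a threshold for the analysis itself gives the full 0.05.

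Two things are at stake. First, one confirmatory test has two thresholds, and in the narrow band between them the choice would be made with the result known. Second, if 0.05 is the level actually applied, the two looks together spend slightly more than 5%. That the interim did not stop the trial does not give the 0.002 back, because the error rate belongs to the design.

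**Working it through.** **Inputs.** From the Sample size section: interim level 0.002, planning level for the final analysis 0.048, interim after 100 patients, final size 2 × 300 = 600, interim incidences 82% and 84% (grade 2 or higher) and 34% and 36% (above grade 2). From the Statistical methods section: alpha 0.05 and a two-sided test.

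**Step 1: the plan's own split.** 0.002 + 0.048 = 0.050. The 0.048 is reproduced as 0.05 less the interim level, an additive (Bonferroni-type) split. With 0.05 at the final look the additive bound is 0.002 + 0.05 = 0.052.

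**Step 2: overall two-look error.** Under the null hypothesis the interim and final statistics Z1 and Z2 are approximately bivariate normal with correlation √(100/600) = 0.408. The overall error is 1 − P(|Z1| < c1 and |Z2| < c2), with c1 = 3.090 for 0.002.

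| Final level | c2 | Additive bound | Overall error |
|---|---|---|---|
| 0.048 | 1.977 | 0.050 | 0.0495 |
| 0.05 | 1.960 | 0.052 | 0.0515 |

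The difference is 0.0515 − 0.0495 = 0.0020, which is the null probability of landing in the disputed band. The largest final level that keeps exactly 5% is about 0.0485, still below 0.05.

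**Step 3: discreteness.** Simulating the chi-squared test itself (50 then 300 per group, 83% event rate in both groups, futility rule ignored) gives 0.0490 with a final level of 0.048 and 0.0508 with 0.05. Hence the ranges of about 4.9 to 5.0% and about 5.1 to 5.2%.

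**Step 4: the second interim grading, if it could also have stopped the trial.** The gradings are nested. At average interim rates of 0.83 and 0.35 their correlation is 0.35 × 0.17 / √(0.83 × 0.17 × 0.35 × 0.65) = 0.33. Adding a second interim route at 0.002 gives an overall error of 0.0513 with a final 0.048 (bound 0.052) and 0.0533 with 0.05 (bound 0.054). A final level of 0.050 − 0.002 − 0.002 = 0.046 restores the additive bound to 0.050; the computed error is then 0.0493.

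**Step 5: cost in power.** For 82% against 84% with 300 per group, the standard error is √(2 × 0.83 × 0.17 / 300) = 0.03067 under the null and √((0.82 × 0.18 + 0.84 × 0.16) / 300) = 0.03066 under the alternative.

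- At 0.048: Φ((0.02 − 1.977 × 0.03067) / 0.03066) = Φ(−1.326) = 9.2%.
- At 0.05: Φ((0.02 − 1.960 × 0.03067) / 0.03066) = Φ(−1.308) = 9.5%.

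The choice of level costs about 0.3 points. The article's stated power of 50% and its 4408 patients are not reproduced as two-sided figures. That is a separate matter, and this point does not depend on it.

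**The case against.** The strongest reply is that 0.05 is a general statement. It closes a section that also covers subgroup, exploratory and surrogate comparisons, it does not name the primary endpoint, and 0.002 and 0.048 add to it exactly. It can be read as the overall level, with the Sample size section giving its split. The authors clearly knew of the alpha cost, since both planning figures use 0.048. This is a fair reading, and it is why the point is minor. The article does not say it, however. The sentence stands without exception in the section that defines the primary test, and a clause would settle the matter. The full protocol may state the level for each look, but the article's two statements would still disagree.

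A reader might go further and infer that the trial will exceed 5%. The documents do not support that as a plain statement. It requires that 0.05 is really applied to the final primary test and that the futility rule earns no credit. The Sample size section says that showing a missing treatment effect would also have ended the study. If that rule is treated as binding on the odds-ratio scale (the printed 0.87 equals the odds ratio of 41/50 against 42/50), the simulated overall error with a final 0.05 at an 83% rate is about 4.4%. Giving no credit is the usual convention, and the article claims none, but it is an assumption.

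A reader might also infer that more than 0.002 was spent because two gradings were tested. The article says that both were compared and that the difference reaching 0.002 would have stopped the trial. It does not say that either grading alone would have sufficed. If either would, a final level of 0.048 would not hold 5% either (about 5.1%).

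The smallness of the effect also stands: only a p-value between 0.048 and 0.05 is affected.

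**Conclusion.** Wrong as written, and minor. The article gives two thresholds for one confirmatory test, and a primary p-value between 0.048 and 0.05 would be read differently under each; under the null hypothesis the chance of this is about 0.2%. Conditional on 0.05 being applied to the final primary test, and with no credit for the futility rule, the overall type I error is about 5.15% by the normal approximation (5.08% in the discrete simulation), against about 4.95% (4.90%) with 0.048. These figures assume looks at 100 and 600 patients and a single interim endpoint that could stop the trial. The estimate, the test, the population and the sample size are unaffected. The text shows neither a decision to ignore the interim look nor an unconditional breach of 5%.

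**What to change.** Amend the Statistical methods section before database lock; the article itself rules out changes to the analysis plan after the database is closed.

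- State that 0.05 is the overall two-sided level, that the final test of the primary endpoint (Clavien-Dindo 2 or higher) is judged at 0.048, and that 0.05 as a per-test level applies only to secondary and exploratory analyses.
- Report the primary risk difference with a 95.2% confidence interval, so that interval and test agree. The article names no confidence level, so this is for consistency and does not correct a stated error.
- State that the 0.002 stopping rule applied to the primary endpoint only. If either interim grading could have stopped the trial, lower the final level slightly to keep 5%; 0.046 does so by the additive bound.

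The cost is a few sentences and, for 0.048 in place of 0.05, about 0.3 points of power at the interim rates.

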### Sub-studies

We expect that the albumin concentration of approximately 20% of the screened patients will drop below 30 g/l. We will also analyze the serum samples of the remaining 80% (when screening for albumin) and will evaluate their primary and secondary outcomes. These data will be collected prospectively to allow secondary and exploratory analyses. All collected serum samples will be analyzed for immature platelets and hypersensitive troponin T concentrations. Planned sub-studies will evaluate the predictive value of these biomarkers on postoperative complications [26, 27]. Furthermore, we will evaluate whether postoperative complications can be detected earlier using the QoR-9 instrument repetitively in this population [28].

## Discussion

SuperAdd is the first clinical trial to investigate the effect of a goal-directed albumin substitution in a surgical population. Although hypalbuminemia is associated with an increased risk of postoperative complications, the substitution of the deficit is controversial due to the large number of clinical conditions causing hypalbuminemia and the diversity of treatment protocols. For instance, albumin substitution in intensive care patients with low albumin concentrations could not improve outcomes, although more stable hemodynamic conditions were reported [10–12]. Likewise, prophylactic albumin substitution for 3 days in surgical patients could not reduce postoperative complications [15]. However, the study could not even prove any surrogate effect of the treatment. The daily substitution was 20 g albumin, which was so meager that the concentrations continued to drop in the 64 treated patients (22.5 ± 4.8 g/l) compared to the 63 control patients (21.9 ± 4.5 g/l), far from enough to show any outcome effects.

Haynes and colleagues analyzed 79 randomized clinical trials about albumin substitution in 2003 [29]. Their metanalyses included 9 studies between 1948 and 1997, in which hypalbuminemia indicated albumin substitution, whereas only one took place in a surgical setting. Nevertheless, the metanalysis reported a consistent dose-dependency and suggested a clinical benefit when the attained albumin concentration exceeded 30 g/l. Recently, the dose-dependency of the effect of albumin substitution was confirmed in cardiac surgical patients. Administration of albumin immediately prior to surgery, aiming to increase the albumin level above 40 g/l, was shown to reduce the risk of acute kidney injury after off-pump coronary artery bypass surgery [14].

The primary outcome for this trial will be the frequency of postoperative complications. We selected the Clavien-Dindo Score [18] in combination with the POMS [17], which has been announced by the COMPAC group as the best choice to measure organ failure and survival in the context of the initiative to define *Standardised Endpoints in Perioperative Medicine (StEP)* [30]. While the Clavien-Dindo Score allows grading of postoperative complications, the POMS systematically addresses which organ system out of nine relevant domains is affected, as well as at which time after surgery it first develops. The combination of both instruments will allow us to properly characterize the complications and to understand how long the treatment effect can be seen. Furthermore, exploratory analyses using each domain as an independent endpoint may allow for the characterization of benefits or harms of the intervention in each of the specified organ systems. For instance, fluid may reduce acute kidney injury while increasing the risk of lung edema.

A major limitation of the study design is the sample size calculation. The prevalence of postoperative complications is given, but not in combination with hypalbuminemia in a general surgical population. Therefore, we performed an interim analysis to better estimate the incidence of complications and to get a figure of potential treatment differences. After 100 patients, the differences were so small that approximately 9000 patients would be required for the study and an expected number-needed-to-treat of 50 [28–232]. The study cohort size to answer the research question was restricted a priori by the regulatory authority to a maximum of 600 patients. In fact, we agree that if there is no beneficial effect of albumin substitution in the cohort of 600 patients with a high risk of complications and given hypalbuminemia, the significant costs of the substitution do not justify further consideration.

We are screening two specific cohorts with an expected high incidence of perioperative hypalbuminemia, due to either an increased loss or a decreased synthesis of albumin. The specified surgical procedures have a transfusion risk > 20% in our hospital and patients with an ASA risk score ≥ 3 are known to produce albumin at a reduced rate [5]. With approximately 1200–1500 patients per year fulfilling the eligibility criteria at the operation units of the Klinikum rechts der Isar, we expect to enroll the 600 patients during a recruitment period of 3 years. Accordingly, approximately 4000 patients will be screened. The nonrestrictive selection guarantees that the patients without albumin screening will most likely not develop hypalbuminemia. Therefore, the high effort and workload promises generalizability of the study results.

### Trial status

The first patient was randomized on 25 June 2017. The interim analysis was completed on 13 November 2018. Recruitment will continue until the complete sample size is achieved, which is expected to be in June 2020.

## Data Availability

The Department of Anesthesiology and Intensive Care of the School of Medicine, Technical University of Munich, will handle the data analysis. The study database, monitoring, and safety reporting are operated by the Munich Study Center (MSZ). Severe adverse events are to be immediately reported to MSZ. A yearly safety report is generated and distributed to the national authority (Paul-Ehrlich-Institute, Bonn, Germany). Datasets can be made available on reasonable request.
